## Abstract

**Background:**

The recent implementation of novel therapies has accelerated progress in pediatric cancer care. Despite the significantly poorer survival of patients in low- and middle-income countries (LMICs), administation complexities and other significant resource barriers have limited the translation of these novel therapies in these regions. This study aims to develop a model that can be used to support the implementation of novel therapies, such as blinatumomab (bispecific antibody therapy for B-cell acute lymphoblastic leukemia [B-ALL]) in LMIC centers, with the long-term goal of developing an implementation framework for similar future efforts.

**Methods:**

In this study, mixed methods will be applied to understand the key contextual considerations that can be accounted for through a training program and prospectively designed implementation activities. The Consolidated Framework for Implementation Research will guide the activities related to implementation evaluation in parallel with a drug donation program. A multidisciplinary research team comprising high- and low-middle income healthcare professionals, industry, and implementation scientists has been assembled with the common goal of improving safe access to blinatumomab. To assess the factors affecting blinatumomab administration, semi-structured interviews with diverse collaborators and quantitative assessments of organizational characteristics will be conducted, together with quantitative and qualitative assessments of feasibility, acceptability, appropriateness, and cost of blinatumomab implementation. A quantitative assessment of stakeholder perceptions of different implementation strategies used as part of the multifaceted approach will also be performed. Finally, we will examine the key domains and processes used and construct the implementation roadmap for translation of novel therapies.

**Discussion:**

This study will rigorously develop an implementation roadmap for translation of novel therapies in low-resource settings. The knowledge gained in the formative assessment will reveal the priority areas and key implementation strategies. Thereby, the resultant roadmap will facilitate future scale-out strategies for novel therapies in LMICs, thus increasing access, building capacity for management, and ultimately improving the care for children in LMICs.

## Contributions to the literature

This study addresses the large survival gap between children with B-cell acute lymphoblastic leukemia (B-ALL) living in high- vs low- and middle-income countries (LMICs) by designing an approach to facilitate the translation of a novel therapy to children in LMICs.Scale-out and sustainability of this initiative require a systematic and scientifically rigorous understanding of the determinants and successful strategies contributing to the effectiveness of resource-adapted and resource-appropriate administration of novel therapies.This study demonstrates the value of collaborator engagement from academic, clinical, and industry partners to go beyond traditional humanitarian efforts and improve care delivery for children with B-ALL in LMICs.

## Background

### Novel therapies in pediatric leukemia

Acute lymphoblastic leukemia (ALL) is the most common type of pediatric cancer and is highly curable with chemotherapy and supportive care. In high-income countries (HICs) like the USA, survival for pediatric ALL is > 90% [1]. While most children with B-ALL survive their disease, outcomes for the 15% with relapsed/refractory disease are historically dismal [2]. Scientific advancements and improved understanding of the biology of ALL have led to the development of novel targeted therapeutic approaches. Blinatumomab (Blincyto®) is a member of the bispecific T-cell engager (BiTE) class and has significantly improved survival for these patients [3]. Blinatumomab was first approved by the US Food and Drug Administration (FDA) as a treatment for relapsed/refractory B-ALL in 2014, then for minimal residual disease (MRD)-positive B-ALL in 2018, and is now increasingly incorporated into frontline ALL treatment. Randomized clinical trials comparing the efficacy of blinatumomab to conventional intensive salvage chemotherapy in pediatric relapsed/refractory B-ALL not only show the improved rate of complete remission, overall survival, and disease-free survival with blinatumomab but also lower rates of adverse events (AEs) [4, 5]. As a result of these novel therapies, the survival rate for pediatric cancers in HICs continues to increase.

### Pediatric cancer survival gap

The global burden of childhood cancer disproportionately affects children living in low- and middle-income countries (LMICs) where more than 80% of children with cancer live [6]. Pediatric ALL survival in LMICs is poor and highly variable by region, from 22% in Africa, 52% in Asia, and 61% in Latin America [1]. This survival gap represents one of the largest disparities in global health; addressing this disparity will require multidisciplinary collaboration at a global level [7].

Poor survival in LMICs is multifactorial and linked to the wide range of resource diversity. In low-income countries, limited supportive care, delayed diagnosis, treatment-related mortality, infection, and abandonment are major barriers to care [8]. However, 75% of the world’s population lives in middle-income countries (MICs) [9], and many have strong healthcare infrastructures, supportive care services, risk stratification with molecular diagnostics, and treat ALL patients with adapted protocols based on published studies from HICs. Despite this, survival outcomes in MICs do not match those in HICs. For example, despite the growth in health system capacity in 2005–2014, outcomes for pediatric ALL in Russia, Mexico, Argentina, Brazil, and Belarus have stalled 10–30% below that of HICs [10]. As reported by international oncology providers in upper-middle-income countries, the lack of access to novel therapies is the main barrier to oncology care in these settings [11] and remains a significant hindrance to incremental improvement that has defined pediatric ALL treatment in HICs over the last 60 years. This highlights a significant problem wherein there is no established, evidence-based method to match the supply and demand of effective novel therapies and translate them into real-world settings such that it operationalizes readiness and optimizes patient safety.

### Translation of novel therapies

Medication cost and skepticism related to the cost-effectiveness of novel therapies are often considered the biggest barriers to translation into LMICs [12]. While blinatumomab is costly, translation has the potential to not only improve survival for the most common type of pediatric cancer but also reduce the need for more toxic, resource-intensive therapies in LMICs. Historic drug donation programs modeled after Glivec International Patient Assistance Program (GIPAP) have addressed medication access limited by cost and logistics; however, their potential impact has been curtailed by inadequately accounting for organizational barriers or medication complexity [13, 14]. Blinatumomab, as with other immunotherapies, is a challenge to administration due to idiosyncrasies that extend beyond traditional pharmaceutical barriers (Table 1) [15–18].

**Table 1 Tab1:** Challenges related to blinatumomab administration and management as well as additional challenges specific to low- and middle-income context

Administration challenges	• Prolonged continuous infusion (1 cycle = 24 h per day for 28 days, typically 2 cycles per patient)• Dedicated intravenous (IV) line• Traditional routine nursing care, such as flushing the infusion line, may push the medicine through the line too quickly and cause an adverse event or overdose• Requires specific types of IV bags, tubing, and ambulatory pump
Management challenges	• Medication initiation requires premedication with steroids and hospital admission (3–8 days) due to the risk of SIRS response. After discharge, patients remain close to care facilities for frequent monitoring in outpatient infusion centers and are often supported by home health services • Interruption in infusion for ≥ 4 h requires readmission to the hospital to restart the infusion • Serious adverse events: cytokine release syndrome, seizure, and other neurotoxicities ○ May result in rapid blood pressure changes, fever, and oxygen requirement ○ May require management in the intensive care unit • Management of adverse events with steroids or expensive medications such as tocilizumab
Examples of additional challenges in LMICs	• Logistical challenges due to medication importation and storage • Limited resources for supportive care (outpatient infusion management, home health capabilities, inpatient bed availability, monitoring labs, ambulatory pumps, IV bags and tubing, medications to manage adverse events) • Transportation challenges impeding rapid return to the hospital setting

*LMICs* Low- and middle-income countries, *IV* Intravenous, *SIRS* Systemic inflammatory response syndrome

Lessons from the treatment of HIV have demonstrated that even complex and expensive treatments are possible when accompanied by innovative treatment models and new investments [12]. Therefore, facilitating the successful adoption of medications like blinatumomab in LMICs requires an approach that addresses cost but also an implementation approach to maximize existing resources and address therapeutic challenges and barriers related to organizational context [19]. Currently, there is no implementation framework for novel pediatric cancer interventions in a global setting. Therefore, we propose INOVATING (Implementing NOVel Agents & Translating Innovation Globally), a non-therapeutic project to facilitate the implementation of novel agents in resource-limited countries to parallel the Blincyto® Humanitarian Access Program (BHAP), a newly established drug donation program.

### Pre-implementation

In December 2019, St. Jude Children’s Research Hospital (St. Jude) formed an academic-based partnership with the blinatumomab manufacturer, AMGEN, and created BHAP. BHAP is not a research endeavor, but akin to GIPAP, developed as a drug-only donation program on a per-patient basis to improve access to blinatumomab for patients in LMICs where it was not commercially available. All components of patient indications, management, and supportive care follow the FDA approval information, supplemented by peer-reviewed publications. These components are further resource-adapted to ensure patient safety and maximal benefit to patients.

The INOVATING program is planned over five phases (Fig. 1).

**Fig. 1 Fig1:**
[figure not shown]
INOVATING 5 phase program plan. The INOVATING program takes place across 5 phases. To date, phases 1–3 are complete, and this proposed protocol outlines the efforts in the evaluation of implementation and effectiveness at LMIC sites. The goal of phase 4 is to create an informed implementation roadmap for novel therapies as phase 5 that can be used to scale out this program to future LMIC sites. LMICs, low- and middle-income countries

Relevant constructs from the Consolidated Framework for Implementation Research (CFIR) were used in the planning and execution and will guide the evaluation phase of this approach [20]. CFIR was selected because it is a determinant-type framework focused on identifying contextual factors that influence the effectiveness and facilitate or hinder implementation, and it has been well operationalized in both high-income and low-middle income settings [21, 22]. This program will use implementation research methodology to understand the impact of determinants and specific strategies on blinatumomab adoption and iteratively integrate knowledge to refine the program and create a resource-informed, reproducible, scalable, and adaptable model, the “Implementation Roadmap for Translation of Novel Therapies,” hereafter referred to as the Implementation Roadmap.

### Phase 1: Stakeholder engagement

Stakeholder engagement has been identified as a strategy to increase the relevance and impact of evidence-based interventions [23]. As the first step in this program, a diverse group of collaborators was assembled to develop a comprehensive understanding of multilevel barriers and facilitators impacting blinatumomab implementation in LMICs. Collaborators represent three main groups: (1) implementation scientists and multidisciplinary pediatric oncology providers from St. Jude with experience in administering blinatumomab and in global health, (2) industry representatives from AMGEN Access to Medicine, and (3) multidisciplinary pediatric oncology providers from LMIC sites, with additional partnerships with a nongovernmental organization (NGO) (e.g., Direct Relief) to facilitate logistics of drug importation and delivery.

Three LMIC centers served as pilot sites for the BHAP program and informed the protocol development. These large, pediatric cancer referral hospitals are located within a common geographic region in India and Pakistan and were selected to tailor materials to specific regional and cultural needs, facilitate a support network between neighboring centers, and promote the growth of regional capacity. Prior to the founding of the BHAP program, these sites had expressed interest in administering blinatumomab by submitting requests to the pharmaceutical company.

### Phase 2: Baseline data collection and program planning

The BHAP Core Team, comprised of multidisciplinary representatives from St. Jude and AMGEN, reviewed and assimilated the institutional administration guidelines, prescribing information, and relevant literature from HICs institutions [15–18] and identified the key administration and management issues for blinatumomab. This helped identify the core domains (indication, dose, and duration) of blinatumomab delivery. The BHAP core team designed a questionnaire to characterize the baseline capacity at LMIC sites, including hospital funding, clinical infrastructure, intensive care ward capacity, nursing care, eligible patient population, standardized operating procedures, medication procurement procedures, advanced treatment experience, and training needs for physicians, nurses, and pharmacists. The 64-question survey was reviewed for content, cultural variations, and ease of use by multidisciplinary international experts. One local physician at three LMIC pilot centers completed the survey, and responses were supplemented through informal discussion with the BHAP core team. The modifiable elements from these preliminary investigations traced back to two CFIR domains, the inner setting (e.g., implementation climate, culture, readiness) and the intervention characteristics (e.g., complexity, adaptability, cost, relative advantage), which are consistent with the findings from a systematic review by Means et al. demonstrating inner setting and intervention characteristics were the most utilized CFIR domains in LMIC settings [22]. Based on BHAP Core Team consensus, recommended best practices for blinatumomab administration were preemptively adapted to include reduced frequency laboratory monitoring, inpatient-only administration, AE management, and standardized bag change schedule. With complex interventions, we expect additional barriers to emerge during implementation and will assess the needs for further adaption based on experience with pilot sites.

### Phase 3: Training program design and delivery

In order to prioritize patient safety and to build knowledge base and skills for the medical team to recognize and respond to AEs, we selected a training program as our primary strategy. The BHAP core team created learning objectives informed by LMIC preliminary capacity assessments and site-specific multidisciplinary training needs to tailor the program to the supportive care capacity of sites. These objectives guided the content creation for a comprehensive, context-adapted training program, including didactic presentations, treatment templates, administration and management guidelines, role-specific workflow materials, and caregiver handouts. Materials were developed by the St. Jude multidisciplinary team, and the content was reviewed by the BHAP core team. Given the COVID-19 pandemic restrictions, we transitioned to an online program, with virtual synchronous sessions and recordings posted to an online classroom on the Cure4Kids platform (http://www.cure4kids.org) along with workflow materials. For pilot sites, all training materials and surveys were administered in English; however, translation and validation will be performed based on the needs of future sites. Training was delivered to 78 healthcare providers (25 physicians, 36 nurses, and 17 pharmacists) and sessions conducted independently for each pilot site as two 90-min live, interactive virtual sessions. The content for the first session focused on general information related to blinatumomab indications, mechanism of action, efficacy, and AE profile and was delivered to the combined multidisciplinary team. The second session were provider-specific, with content focused on the management issues related to roles. These didactic sessions were facilitated by a St. Jude pediatric oncologist, a nurse, and a pharmacist, with time for group discussion. The training meetings highlighted the importance of prompt response when managing patients on immunotherapy and modeled risk-reducing communication techniques between providers. After the multidisciplinary team attended the two training sessions, centers could apply for blinatumomab on a per-patient basis, at which point the medication would be shipped and sites could begin administration.

### Study aims and research questions

The overall goal of the next stage, phase 4 (Fig. 1), of the INOVATING program is to formally evaluate the key determinants of novel therapy administration in a resource-limited setting and then develop a generalizable “Implementation Roadmap” to reduce disparities in time to translation and facilitate less costly implementation of effective, newer treatments with lower toxicity profiles.

The aims of this study are to (1) conduct a formative evaluation to assess the determinants that influence the implementation of blinatumomab in LMIC settings; (2) evaluate how different components of the multifaceted strategy package influence implementation, provider knowledge, competence, clinical effectiveness, and safety of drug preparation, administration, and management; and (3) use data collected to inform an “Implementation Roadmap” to speed the translation of blinatumomab in other lower resource settings.

This study seeks to answer the following research questions: (1) Can blinatumomab be adapted for LMIC settings, and is it feasible, acceptable, and appropriate? (2) How does an adapted multidisciplinary training program affect these implementation outcomes? (3) Are there contextual factors (readiness, capacity, perceived complexity) that correlate with successful implementation? (4) What key strategies facilitate implementation and are they similarly prioritized by different stakeholder groups? (5) What is stakeholder satisfaction with this implementation-guided approach? (6) Is the effectiveness of this adapted administration of blinatumomab similar to that documented in high-income settings?

### Methods

This convergent, mixed methods study addresses stated research questions based on the CFIR framework. Table 2 lists data sources. Qualitative methods include open-ended questions, stakeholder interviews, and meeting notes. Quantitative methods include surveys and secondary clinical and costing data. Methods will define the barriers and facilitators and explore the impact of these barriers and strategies on implementation outcomes, including feasibility, acceptability, appropriateness, and clinical effectiveness of blinatumomab in resource-limited settings using an effectiveness-implementation hybrid type 2 case series design. Due to ethical implications and prioritization of patient safety in these centers, randomization is not possible.

**Table 2 Tab2:** Study data sources including data collector, data collection method, correlation to specific CFIR domain, and target study participant. Matrix of data collection methods

Type of data	Data collectors	Data collection method	CFIR domain	Study participants
Primary data	BHAP core team	Hospital assessment questionnaire	Inner setting	Pilot center physician champion
	St. Jude research team	Provider knowledge assessment	Inner setting	Multidisciplinary pilot center providers
		Organization Readiness for Implementing Change (ORIC)	Intervention characteristics	Pilot center implementation team
		Implementation Climate Scale (ICS)	Inner setting	Pilot center implementation team
		Complexity of intervention assessment	Intervention characteristics	Pilot center implementation team
		Implementation outcome surveys (Feasibility of Intervention Measure, Acceptability of Intervention Measure, Intervention Appropriateness Measure)	Intervention characteristics	Pilot center implementation team
		Strategy ranking survey	Process	Pilot center implementation team
		Stakeholder interviews (barrier assessment, informed adaptation of patient eligibility criteria and training materials, strategy prioritization, and assessment)	Inner setting Process Intervention characteristics Outer setting	Key stakeholders
		Meeting notes	Process	Key stakeholders
		Group interview (strategy analysis, feedback on training strategy, implementation outcome, team dynamics, identifying unanticipated challenges, and adaptation of implementation, provider satisfaction)	Inner setting Process Intervention characteristics	Pilot center implementation team
Secondary data	Local site providers	Medication interruption record	Intervention characteristics	Blinatumomab recipients
	Local site providers	Adverse event reporting, severity, and number of events	Intervention characteristics	Blinatumomab recipients
	Local site providers	Disease outcomes (MRD status, remission status, proceed to transplant, mortality)	Intervention characteristics	Blinatumomab recipients
	Local site providers	Participant satisfaction	Intervention characteristics	Patient and family
	Local site providers	Baseline patient characteristics	Intervention characteristics Inner setting	Blinatumomab recipients
	Local site providers	Delivery cost of blinatumomab	Intervention characteristic	Blinatumomab recipients
Process indicators	St. Jude research team	Attendance of training sessions, utilization of web-based resources, and proportion of patients enrolled in the BHAP program	Process	Pilot center providers

*BHAP* Blincyto® Humanitarian Access Program, *CFIR* Consolidated Framework for Implementation Research, *MRD* Minimal residual disease

The results will yield an in-depth understanding of key determinants and prioritization of key implementation strategies, which will be assembled into a framework to facilitate real-world scalability of blinatumomab in future centers.

### Collaborators and setting

This study is being conducted in collaboration with BHAP. LMIC sites where blinatumomab is not commercially available were identified and stratified into two groups: group 1, characterized by established pediatric cancer units, experienced bone marrow transplant centers, and specialized chemotherapy pharmacists; group 2, characterized as developing pediatric cancer and bone marrow transplant programs (autologous only or none) and overlapping nursing and pharmacist responsibilities.

The experience in the three group 1 pilot sites will inform the characterization of the future grouping in the model to facilitate expansion into future sites.

### Study participants

The training program will be administered to all multidisciplinary pediatric oncology staff at each site. Evaluation data will be collected from multiple stakeholders: LMIC pediatric oncology staff, pilot site implementation team, pharmaceutical industry representatives, and multidisciplinary academic providers at St. Jude. The study will also collect secondary data from ~ 50 children enrolled in the BHAP program who received blinatumomab. Table 3 describes the inclusion criteria.

**Table 3 Tab3:** Inclusion criteria for primary and secondary data collection

**Primary data study participant group**	**Primary data inclusion criteria**
Local site physician champion	Submit an application for BHAP program enrollment
Multidisciplinary local site pediatric oncology staff	Attend both 90-min synchronous training sessions or watch session recording online
Local site implementation team	Will include a minimum of 2 physicians, 2 nurses, and 1 pharmacist at each LMIC site, who attended both training sessions and participated in frontline management of patients receiving blinatumomab in the inpatient setting
Key stakeholders	Representatives from the pharmaceutical company actively involved in the drug donation program Representatives from St. Jude actively involved in the BHAP program LMIC site implementation team
**Secondary data study participant group**	**Secondary data inclusion criteria**
Patients	Satisfy BHAP program enrollment criteria to receive blinatumomab, parental consent to receive blinatumomab (obtained by a local physician), and initiate blinatumomab infusion

*LMIC* Low- and middle-income countries, *BHAP* Blincyto® Humanitarian Access Program

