### Study recruitment and informed consent

This protocol was approved by the St. Jude Institutional Review Board and will be reviewed by LMIC local participating sites’ ethics committees. Recruitment will occur after the completion of the baseline BHAP administrative application and the hospital assessment questionnaire for the drug donation program. Participation in the BHAP program does not necessitate participation in this implementation research study, and AMGEN will not be involved in recruiting participants for the implementation study. If sites agree to participate, the baseline information collected for the BHAP program enrollment will be included in the study.

At LMIC sites, all pediatric oncology staff who participate in the training program will complete a brief knowledge assessment survey. However, the remainder of the implementation evaluation will occur through a site-specific implementation team. This team will be identified by the site PI and consists of multidisciplinary members who have demonstrated organizational leadership in the implementation of blinatumomab and will contain at least two physicians, two nurses, and one pharmacist. This group selection will satisfy pragmatic constraints due to limited resources and time in LMIC settings but will also provide rich representation within and between different provider roles within an institution and thematic saturation across multidisciplinary experts. These providers will give consent to complete additional surveys and participate in semi-structured interviews.

Secondary data related to implementation costs and routine clinical care will be collected. Deidentified patient information will be required to confirm patient suitability for participation in the BHAP program and for routine monitoring during medication administration and clinical care.

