### Aim 1: To conduct a formal assessment to characterize determinants that influence blinatumomab implementation in LMICs

For aim 1, this study will use mixed methods to evaluate the hypothesis that barriers related to inner setting and intervention characteristics impact the implementation of blinatumomab in LMICs. This will include the assessment of (1) capacity, (2) key barriers (readiness, climate, intervention complexity, cost), and (3) perceptions of leading indicator implementation outcomes (feasibility, acceptability, and appropriateness) from multiple stakeholders. For the three pilot sites, implementation assessments will occur 1 year after the training; however, for future sites, these will be part of the upfront baseline assessment. Assessments will be repeated at 3, 6, and 12 months post-training to characterize changes in perceived barriers and implementation outcomes over time (Table 4).

**Table 4 Tab4:** Assessment administration time points, target respondents, and frequency. Measurement tools including the type of data, key respondents, frequency, and time points of administration

Survey topic	Method	Respondent(s)	Frequency	Time point(s)
**Hospital assessment questionnaire**	QUAN	LMIC site physician champion	1 time	Prior to BHAP enrollment
**Complexity assessment**	QUAN	Implementation team	4 times	Pre-training, 3 and 6 months, and 1-year post-training
**Implementation Climate Scale (ICS)**	QUAN			
**Organization Readiness for Implementing Change (ORIC)**	QUAN			
**Acceptability of intervention (AIM)**	QUAN			
**Intervention Appropriateness Measures (IAM)**	QUAN			
**Feasibility of Intervention (FIM)**	QUAN			
**Knowledge assessment: nurses**	QUAN	All nurses	4 times	Pre-training, 3 and 6 months, and 1 year post-training
**Knowledge assessment: pharmacy**	QUAN	All pharmacists		
**Knowledge assessment: physician**	QUAN	All physicians		
**Training material feedback survey**	QUAL	Implementation team	1 time	3 months post-training (after the 1st patient received blinatumomab)
**Semi-structured group interviews:** **1) Training program feedback and site-specific barriers** **2) Site-specific fidelity vs adaptation**	QUAL	Implementation team	2 times	3 months post-training (after the 1st patient received blinatumomab) and 12 months post-training
**Implementation strategy feedback**	QUAN	Key stakeholders (implementation team, industry, St. Jude)	1 time	Annual review
**Program evaluation group interview**	QUAL			
			1 time	Annual review

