Descriptive statistics will be used to characterize the barriers and facilitators to blinatumomab implementation in LMICs. This will include describing core components of implementation, such as site infrastructure, climate, readiness, and intervention complexity. The survey will be summarized by frequency tables and cross-tabulation to study any associations. The chi-squared and Fisher’s exact test will be used to assess the associations. Comparisons will be made with assessments of barriers done over time (pre-training; 3, 6, and 12 months post-training). Univariate and multivariable logistic regression analysis will be used, as appropriate, to study the correlations among scores of clinical infrastructure, readiness, climate, and intervention complexity with implementation outcomes (feasibility, acceptability, and appropriateness) within and across institutions. Collectively, this information will be used to understand barriers and site-specific adaptations to modify the strategy approach and training program for medication delivery.

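### At future sites the implementation team is defined by events after training, yet must complete six surveys before training

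*Protocol article*

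**What the plan says.** Three places in the protocol article fix who answers the implementation surveys and when.

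- **Eligibility.** Table 3 (Study participants) requires at least 2 physicians, 2 nurses and 1 pharmacist per site, "who attended both training sessions and participated in frontline management of patients receiving blinatumomab in the inpatient setting". Study recruitment and informed consent adds: "This team will be identified by the site PI", and describes it as made up of "multidisciplinary members who have demonstrated organizational leadership in the implementation of blinatumomab".
- **Role.** All trained staff complete the knowledge survey, but "the remainder of the implementation evaluation will occur through a site-specific implementation team".
- **Timing.** Table 4 (Aim 1) names the implementation team as respondent for the complexity assessment, ICS, ORIC, AIM, IAM and FIM, four times: "Pre-training, 3 and 6 months, and 1-year post-training".

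The Aim 1 text treats the two kinds of site differently: "For the three pilot sites, implementation assessments will occur 1 year after the training; however, for future sites, these will be part of the upfront" (the sentence goes on to call this the baseline). The Aim 1 analysis text uses the early time point: "Comparisons will be made with assessments of barriers done over time (pre-training; 3, 6, and 12 months post-training").

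**The concern.** Every criterion for joining the team looks back on something that happens at or after training. The first survey the team must complete comes before training. The definition therefore cannot pick out the people who are to answer at baseline.

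The baseline has a use. Aim 1 sets out to describe change in both barriers and implementation outcomes over time. Research question 2 concerns the effect of the training program on the implementation outcomes, and Table 6 lists FIM, AIM and IAM among its data sources. If one group answers before training and a later-qualified group answers afterwards, a difference between time points need not mean that anyone's view changed.

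There is a second consequence. Staff who were trained but missed a session, left, or never cared for a patient on the drug fall outside the definition. So does every member of staff at a site that trained but never treated. This also narrows the range of sites available to research question 3, which looks for contextual factors that correlate with successful implementation.

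**Working it through.** No sample size or power is stated for these surveys and none is needed. The check is one of order in time, for a future site.

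**Step 1. When can each criterion first be met?**

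| Criterion | Source | Earliest time it can be met |
|---|---|---|
| Attended both sessions | Table 3 | End of the second session |
| Took part in inpatient care of treated patients | Table 3 | After the site's first patient starts |
| Has shown leadership in the implementation | Recruitment section | Once there is implementation to lead |

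On drug supply, the Phase 3 section says: "After the multidisciplinary team attended the two training sessions, centers could apply for blinatumomab on a per-patient basis". That describes the pilot sites; I assume that future sites follow the same order. The baseline conclusion does not need this assumption, since the attendance criterion alone rules everyone out before training.

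**Step 2. Compare with the survey schedule in Table 4.**

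| Time point | Staff who can meet Table 3 |
|---|---|
| Pre-training | 0, by definition |
| 3 months | 0 if the site has treated no patient; otherwise some |
| 6 and 12 months | Same condition |

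So 1 of the 4 time points has no eligible respondent at any future site, for all 6 instruments. The 3-month point has none at a site with no treated patient. Table 4 makes the 3-month group interview and the training feedback survey wait for the first treated patient, but puts no such condition on these six surveys.

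**Step 3. What a change of respondents does.** In a minimum team of 2 + 2 + 1 = 5, each member carries 1/5 of the team mean. If k members are replaced by people whose scores differ from theirs by d on average, the team mean moves by (k/5) × d with nobody changing their opinion. The document gives neither k nor d, nor the sign of d, so this shows the mechanism and is not an estimate.

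**Step 4. Pilot sites.** Their implementation surveys take place 1 year after training, when past-tense criteria can be met. There is no conflict with a baseline, because none is planned for them. On how selected the team is: the stated number trained reproduces as 25 + 36 + 17 = 78, and minimum teams give 3 × 5 = 15, or 15/78 = 19%. Five per site is a minimum, so the actual share may be larger.

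**Step 5. Does any other part of the plan name the team earlier?** Table 5 places the organising of clinician implementation teams in Phase 2, ahead of Phase 3 training. That does not fit the criteria in Table 3 and the recruitment section.

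**The case against.** The strongest reply is that this is wording carried over from the pilot phase. The criteria suit the pilot sites, Table 2 names the pilot center team as respondent, and Table 5 has teams organised before training. Recruitment follows the program application and the hospital questionnaire, which Table 4 places before program enrolment, so a future site could name and survey its team in time. Selecting a small informed team is also disclosed and justified by limited time and resources, and the analyses are formative and largely descriptive.

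Much of this stands, and it limits the point. Four stronger readings are tempting and are not supported:

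- **That the whole study lacks a usable baseline because of eligibility.** The conflict concerns future sites. The pilot sites have no baseline because of when they are surveyed.
- **That a baseline cannot be obtained.** Table 5 suggests that it can. The baseline group is undefined, not out of reach.
- **That later scores come from selected successes and are too high.** The criteria select on participation and leadership, not on a good result. Staff who have run 28-day infusions might rate complexity higher or feasibility lower than staff who have not. Multiplying an assumed gap by the 81% of pilot trainees outside a minimum team would give a figure, but only for an invented gap, and only if the target were the mean of all trained staff.
- **That the 15 minimum pilot members supply all implementation-outcome data.** Table 6 also draws on cost data and on the program evaluation interview, which includes industry and academic stakeholders.

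What the reply does not remove is the contradiction. Table 5 is described as a retrospective mapping of strategies and does not redefine the respondents. Limited resources justify a small team, but not one whose membership depends on later events: naming the same number of people earlier takes no more respondent time. Whether leadership should be a criterion at the pilot sites, and how their response counts are reported, are matters of sampling preference and reporting detail.

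**Conclusion.** The point holds for future sites. As written, no one qualifies for the pre-training survey, and no one qualifies at 3 months where no patient has been treated. If membership is settled later, respondents are chosen on engagement after baseline, and the comparison over time used for research question 2 has no fixed cohort. The size of the defect is one undefined time point of four on six instruments, plus a second that depends on treatment having started. The effect on scores is unknown in direction and size. The conclusion rests on reading Table 3 and the recruitment section literally; the 3-month part also rests on no patient having been treated by then. Pilot results are untouched by the baseline conflict but should be read as post-training scores from a selected team.

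**What to change.** For future sites, reword Table 3 and the recruitment section so that the team (at least 2 physicians, 2 nurses and 1 pharmacist) is named before training, by role and expected involvement. This brings both into line with Phase 2 of Table 5. Survey the same named members at all four time points, whatever their later attendance or patient contact, and record attendance, patient contact and leadership as descriptors. Describe the pilot-site scores as post-training only.

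The cost is a change of eligibility wording, with no added surveys. The downside is small: some named members will have little hands-on experience when they answer, and the descriptors will show which. The change should be made before expansion, since a pre-training survey that is missed cannot be recovered.
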